## EXPECTED RESULTS, POTENTIAL DIFFICULTIES, AND ALTERNATIVE STRATEGIES

The importance of this study design is that it mimics real world use of ECs. These devices are being widely promoted as an alternative form of smoking cessation with many switching to but not weaning from them. This is in part because of the unproven statement that tobacco-free products are safer and their indoor use is unregulated, which theoretically allows an increased nicotine exposure. For the trial, we chose to study the most commonly used EC type and the most frequently used e-liquid mix of PG and VG (50:50).

The effects of EC on airway TGF- $\beta$  and ion exchange are hard to predict at this point. We expect that the presence of nicotine will significantly affect NPD similar to what regular tobacco cigarettes do. If the PG:VG mix has no local toxic effects in this subacute exposure (determined in other aspects of the study), it is possible that TGF- $\beta$  levels will improve as the duration of tobacco cigarette abstinence increases (nasal samples), but nicotine could maintain these levels seen with smoking. If this is the case, it will provide valuable information that replacing regular cigarettes with EC is not less toxic or harmful as is generally perceived.

The initial phase of screening more smokers than required to complete the analysis is necessary to avoid performing semi-invasive and time consuming procedures such as NPD in subjects likely to relapse back to tobacco use, as well as to avoid the phase of dysregulated airway inflammation that may occur when smoking cessation occurs (55). Although the subjects undergoing study procedures will do so after 4 weeks of already using ECs, we expect to still detect significant differences in the data collected 3 months later if there is cumulative toxicity in the long term.

Although we do not anticipate major problems in subject recruitment at the VA, in case of slow enrollment, we will extend study invitations to the 10 clinic-base outpatient centers that are part of the Miami VA health system. These clinics nearly double the Miami VA population to close to 50,000 subjects. We do not expect complications executing any of the study procedures. Assurance of tobacco cessation will be monitored objectively every 2 weeks in different types of samples (exhaled air and blood) to maximize detection of non-compliance. Although it is possible that some subjects may elude these surveillance tests at a certain time, it is unlikely that this may occur for every checkpoint. If there is suspicion that a subject may be smoking, based on interview or equivocal test results, we will opt to exclude the subject from the study and continue expanding enrollment. If dropout in the EC use arm is higher than anticipated, we will recruit more subjects to reach the final number of 30 completing the study on ECs. This is unlikely since there is a very high adherence to ECs in a nicotine replacement environment for the relatively short total duration of 3 month (49).

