## EXPERIMENTAL APPROACH

The study will evaluate the effects of inhaling EC vapor containing nicotine when used as a tobacco replacement tool. **By using active cigarette smokers as a comparator group, the study will increase our knowledge of whether the use of ECs is more or less harmful than continuation of tobacco smoking.** This study will examine the *in vivo* effects of EC vapors in nasal ion transport and TGF- $\beta$  levels as well as in serum inflammatory biomarkers.

As the primary endpoint, nasal ion transport will be assessed by nasal potential difference (NPD), which measures the voltage potential resulting from epithelial ion fluxes (both Na+ absorption and Cl and K+ secretion, see 37, 38) at the mucosal surface *in vivo*. In normal airway epithelia, Na+ absorption is the primary ion transport activity so that the resulting airway surface potential difference is negative with reference to the interstitium (39). Ion transport across nasal epithelia is representative for findings in distal airways (40, 41).

We also believe that NPD is a reasonably sensitive and minimally invasive biomarker for this study as discussed below. We will use NPD as a primary endpoint because changes in most clinical parameters will only be seen after months or even years of exposure. For that particular reason, there is a recent surge to find alternative biomarkers that may be used as surrogate endpoints in shorter clinical trials. Since NPD directly measures the changes in ion transport expected to influence mucociliary clearance (MCC) and therefore overall outcome and since changes of NPD measurements are indirectly linked to lung function changes and MCC in trials with cystic fibrosis patients (44, 45), we believe that NPD lends itself as a reasonable surrogate for MCC for this clinical trial.

As secondary endpoints, we will also measure TGF- $\beta$  levels in nasal secretions and expression in nasal cells to correlate these with the level of CFTR and CaCC-mediated Cl conductance (CFTR is known to show decreased function with elevated TGF- $\beta$ ) (42, 43). In addition plasma

samples will be collected to study systemic markers of inflammation as well as toxic substances that may result from vaping and smoking

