Inhaled nicotine dose calculation: We will match the subjects’ daily nicotine dose when switching from tobacco smoking to EC vaping. A Kentucky 3R4F research cigarette contains ~0.7 mg nicotine (<http://www2.ca.uky.edu/refcig/3R4F%20Preliminary%20Analysis.pdf>) and is consumed in 9 puffs. The equivalent of 1 pack per day (180 puffs, 14 mg of nicotine) would be an eVic® 1.2 ml cartridge containing 12 mg/ml of nicotine (cartridges are available as 6, 12, 18, 24, 36 and 48 mg/ml). One cartridge provides 180-200 puffs. Given that nicotine content in “e-liquids” is variable, we expect subjects to adjust their number of puffs or cartridges a day according to their needs or preferences. Since the EC chosen will count the puffs, we will have a record of use.

Statistical Analysis: An  $n = 50$ , 30 EC users and 20 smokers, gives us a power of >98% for detecting a difference in TGF- $\beta$  levels. We will analyze NPD parameters as described above. Results will be adjusted to nicotine exposure (urinary nicotine and cotinine levels) and inhalation (EC puffs per day).

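### The protocol would read TGF-β staying at smoking levels as evidence that e-cigarettes are no less harmful, but the study is sized only to detect a difference

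*Protocol*

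**What the plan says.** Expected Results, Potential Difficulties, and Alternative Strategies first calls the effects of EC on TGF-β and ion exchange hard to predict. For NPD it then states an expectation: "We expect that the presence of nicotine will significantly affect NPD similar to what regular tobacco cigarettes do". For TGF-β it leaves two outcomes open. Levels may improve with longer tobacco abstinence, "but nicotine could maintain these levels seen with smoking". If the second outcome occurs, the protocol says "it will provide valuable information that replacing regular cigarettes with EC is not less toxic or harmful as is generally perceived".

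The sample size is justified in the Statistical Analysis paragraph under Experimental Design: "30 EC users and 20 smokers, gives us a power of >98% for detecting a difference in" TGF-β levels. No difference, SD, significance level or test accompanies that figure, and no power is given for NPD.

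Experimental Approach ranks the endpoints the other way round from the power statement: "As the primary endpoint, nasal ion transport will be assessed by nasal potential difference (NPD"), and "As secondary endpoints, we will also measure TGF"-β levels.

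Experimental Design sets out a comparison of changes between smokers who switch and smokers who continue. In Table 1 the first NPD, nasal lavage and nasal brushing are at V5, after the four-week transition phase. Smoker controls enter the stability phase directly.

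**The concern.** The quoted inference runs from EC users looking like smokers to EC being no less harmful. That is a claim of similarity, or more exactly a claim that a meaningful benefit has been ruled out. Power to detect a difference does not support such a claim. A study can have high power for a very large difference and still be unable to exclude a moderate one.

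Experimental Approach makes the relative harm of EC and continued smoking the study question, and the Importance of the Knowledge section says the results may lead to regulation. If a null result were read in the way the paragraph suggests, a real benefit of switching that the study was too small to see could be reported as absent.

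The timing of the first nasal sample adds to this. Any fall in TGF-β during the first four weeks on EC is already in the EC group's baseline. Similar changes in the two groups over the next 12 weeks would then be compatible with a benefit that came before the first measurement.

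**Working it through.** **Inputs**
- 30 EC users and 20 smokers (Statistical Analysis paragraph).
- Stated power above 98% for TGF-β (same place).
- Assumed, because the protocol does not give them: an unadjusted two-sample t comparison with 48 degrees of freedom, two-sided 5%. All differences are in SD units of whatever outcome is analysed. If changes are analysed, the SD is that of the change.
- Margins are also assumed, so a range is shown.

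**1. The protocol's own figure.** The power above 98% cannot be reproduced without a difference and an SD. It can be solved backwards.
- Standard error = √(1/30 + 1/20) = √0.0833 = 0.289 SD.
- With the noncentral t distribution, 98% power requires a true difference of about 1.18 SD (two-sided 5%) or 1.08 SD (one-sided 5%).

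If the stated power is right, it refers to a very large difference.

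**2. Precision.** The 95% half-width is t(0.975, 48) × SE = 2.011 × 0.289 = 0.58 SD. An observed difference of exactly zero would leave open an EC benefit or harm of up to about 0.58 SD.

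**3. Chance of missing a real benefit** (two-sided 5%, noncentral t).

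| True EC benefit (SD) | Power | Non-significant |
|---|---|---|
| 0.5 | 40% | 60% |
| 0.8 | 78% | 22% |
| 1.0 | 92% | 8% |

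**4. What a supportable claim would need.** The claim is one-sided: the interval must exclude an EC benefit larger than a margin m. With no true difference and one-sided 0.025, power = P(T > 2.011), where T is noncentral t with 48 df and noncentrality m/0.289.

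| Margin m (SD) | m/0.289 | Power at 30 vs 20 |
|---|---|---|
| 0.5 | 1.73 | 40% |
| 0.7 | 2.42 | 66% |
| 0.8 | 2.77 | 78% |
| 0.9 | 3.12 | 86% |

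80% is reached at about 0.83 SD. For scale, a 0.5 SD margin at 80% power would need 80 EC users and 53 smokers, 133 in all.

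**5. Baseline.** No arithmetic is possible, because the protocol gives no figure for the change in the first four weeks. Write the EC group's full change since switching as (change over weeks 1 to 4) + (change over the stability phase). The two nasal samples capture only the second term. Equal second terms in the two groups say nothing about the first.

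**The case against.** The strongest reply is that the sentence is a conditional interpretation in an expected-results section and not a decision rule. Its condition is that levels are maintained, not that a test is non-significant. That is correct. A reader might infer that the protocol commits itself to treating p > 0.05 as equivalence, but nothing in it says so. The difficulty that remains is that the only inferential basis offered is power to detect a difference, so the text gives no way to establish that levels were maintained.

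Other stronger readings also fail:
- **No difference is the result the investigators most expect.** For TGF-β the paragraph leaves both improvement and maintenance open. Similarity is an expectation only for NPD.
- **The sentence about harm rests on NPD.** It follows from TGF-β, a secondary endpoint. A criterion in mV alone would not govern it.
- **The missing margin is itself the error.** A margin may properly be set in a statistical analysis plan that is not shown. The finding is the conclusion the protocol itself draws.
- **The lack of a non-smoker group is a defect.** This is a sub-study of a larger project whose proposal includes non-smokers, so it is a choice of scope.
- **Power for the claim is close to nil.** Two-sided equivalence testing gives only about 7% to 8% at a 0.5 SD margin, but the claim needs only the benefit side excluded, for which power is 40%.

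A null result is also not worthless. If the stated power is right, it argues against a TGF-β difference of roughly 1.1 to 1.2 SD or more. On the baseline, the protocol openly acknowledges the four-week delay and gives reasons for it. The point here is only what that timing does to this inference.

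**Conclusion.** The concern holds as a fault in a stated interpretation. The protocol would take maintained TGF-β as information that switching is no less harmful, in a study justified only by power to detect a difference. At 30 versus 20, a null result leaves benefits of up to about 0.58 SD open, and a true benefit of 0.5 SD would go undetected about 60% of the time. The post-switch baseline means that similar changes could also conceal an early benefit.

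The figures rest on an unadjusted two-group comparison at two-sided 5%, expressed in SDs of the analysed outcome. The planned adjustment for nicotine exposure and inhalation could alter the precision in either direction, and the protocol gives nothing from which to estimate by how much. The logical point does not depend on these assumptions; its size does.

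**What to change.** Amend the paragraph in Expected Results to say the following:
- A non-significant EC-versus-smoker difference in TGF-β or NPD is inconclusive and will be reported with its confidence interval.
- EC will be described as no less harmful on a marker only if that interval excludes an EC benefit larger than a margin fixed before the data are seen. The margin is given in assay units for TGF-β and in mV for NPD.
- Any such statement is limited to the measured marker over the 12-week stability phase, since the first four weeks on EC precede the first nasal sample.

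Add a note that with 30 and 20 subjects and no true difference, 80% power for this one-sided 0.025 rule needs a margin of about 0.83 SD. If a margin that wide cannot be defended as unimportant, report the interval and make no such claim.

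The change is to wording only and needs no further subjects or procedures. The cost is a weaker claim if the result is null.

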## HUMAN SUBJECTS

THE STUDY MEETS THE DEFINITION OF HUMAN SUBJECTS RESEARCH AND THE DEFINITION OF A 'CLINICAL TRIAL'. WILL BE REGISTERED ON [WWW.CLINICALTRIALS.GOV](http://WWW.CLINICALTRIALS.GOV)

### 1. Risks to the Subjects

A) Human Subjects Involvement and Characteristics: We will enroll active smokers older than 18 years, who actively smoke and have a smoking history of at least 5 pack-years. These subjects should not be currently using ECs but should be willing to replace tobacco cigarettes to ECs. All subjects will undergo lung function testing to exclude chronic obstructive pulmonary disease, as this condition may not only increase the risk of procedures but also impose additional inflammatory confounders. Exclusion criteria include the presence of airflow obstruction ( $FEV_1/FVC < LLN$ ), other concomitant inflammatory pulmonary disorders (i.e asthma), subjects with known pulmonary malignancies, subjects with prior thoracic surgery and subjects that used oral corticosteroids or antibiotics within the prior 3 months, subjects with allergies to study medications and subjects incapable of providing informed consent. Subjects must be in stable condition. Considering that about 75% will not be able to stay abstinent from tobacco cigarette smoking, we expect to screen 120 subjects, who meet these criteria, to be able to have 30 subjects who will complete all study procedures 3 months apart. In addition, we will enroll 20 active smokers unwilling to quit tobacco smoking but willing to undergo the study procedures using the same exclusion criteria. Since these trials will be performed at the Miami Veterans Affairs (VA) Medical Center, we expect that subjects will be >90% men, 20% Hispanic and 25% African American.

B) Sources of Materials: The following are the procedures that will be performed:

Collection of nasal lavage fluid: Nasal lavage fluid will be used to measure changes in epithelial inflammatory cytokines. The lavage will be performed using saline pre-warmed to 37°C. The subject will keep the head bent forward with the face held horizontally, while the left nasal cavity is filled with saline, using a 10 ml syringe connected to the nostril via a short tube and a nasal olive. After 5 minutes approximately 5 ml of the saline is recovered by aspiration. The samples will be centrifuged to remove cellular debris and aliquots of the supernatants stored at -20°C in microcentrifuge tubes until analysis.

Harvesting of nasal epithelial cells will be performed following the nasal lavage to obtain nasal epithelial cells for the assessment of nasal epithelial cytokine mRNA expression. For this, nasal mucosal cells will be harvested from the right nasal cavity by a gentle nasal brushing using a 5.5 mm diameter nylon brush (Doft AB, Östhammar, Sweden). The brush will be immediately placed in a tube containing physiological saline and twirled for 3-5 seconds. Cells will be centrifuged and the pellet re-suspended in *RNAlater*® and stored at -80°C for later analysis.

Nasal Potential Difference (NPD). Clean, double lumen nasal catheters with an external diameter of 2.5 mm will be used for measurements. One lumen will be filled with freshly prepared agar; the other lumen will be used for perfusion with different solutions. The agar catheter and subcutaneous bridges (metal butterfly needle system) will be made immediately prior to use by warming 3% agar gel and injecting the solution into the catheter. They will be attached to 3M KCl/calomel reference electrodes (Baxter; Deerfield, IL) and connected to a bioamplifier system (AD Instruments; Colorado Springs, CO) for measuring and recording. The catheter tip will be fixed at the location of the most negative potential in the area under the inferior meatus. The test will be initiated after a stable value ( $\pm 0.5$  mV over 30 s) is obtained using perfusion with Ringer solutions. Then, the nose will be rinsed with different solutions containing amiloride (to block ENaC), no chloride (increase CFTR conductance), isoproterenol (activate CFTR) and ATP (stimulate CaCC). In the other nostril, the same experiment will be repeated, but we will attempt to maximize the CaCC signal. For this, we will initially also block ENaC with amiloride, and

equilibrate the chloride concentrations with perfusion of the nasal epithelium with chloride free solution. From there, we will not stimulate the CFTR with isoproterenol, but will directly use ATP to increase the intracellular calcium concentration and activate CaCC. The rinsing with chloride free solution is necessary to not confuse passive chloride flow through CFTR based on gradient differences with flow through ATP activated CaCC.

Blood samples will be obtained to measure venous COHb, inflammatory markers and toxic metabolites. 2 standard EDTA 5 ml tubes will be collected to harvest plasma. A 1 ml heparinized syringe will be used for the venous COHb.

Pulmonary Function Testing will be performed according to American Thoracic Society recommendations if not done within 1 month prior to enrollment. Participants will be asked to refrain from using short-acting bronchodilator drugs for at least 4 hours before testing. Lung volumes and DLCO will also be performed following ATS recommendations. Height, weight and oxygen saturation will be measured prior to these tests.

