#### EXPERIMENTAL DESIGN

The design is a smoking replacement trial, in which we will compare changes in upper airway ion transport and inflammation in smokers who switch to EC vaping versus subjects that continue to smoke tobacco cigarettes. In addition, we will use the trial design to evaluate the feasibility of using the EC as a means to quit tobacco use.

*Study population/recruitment.* We plan to study the effects of continuous EC vaping (3 months) in 30 active smokers that successfully switch to ECs (a smoking replacement trial). For this, we plan to enroll approximately 200 active smokers (screening phase), expecting that only one fourth will be able to stay abstinent from tobacco and keep exclusively vaping the ECs after a month. The 30 subjects who can remain tobacco-smoke free for the initial 4 weeks will undergo the study procedures, as >90% of them are likely to remain on ECs for the next few months (49) (as opposed to what is observed in a smoking cessation trial (48)). Twenty additional smokers who wish to continue to smoke will be enrolled as well for the comparator group. Subjects that actively smoke and have a history of at least 5 pack-years will be invited to participate. Exclusion criteria include HIV, marijuana use, COPD, asthma and other concomitant inflammatory pulmonary disorders, subjects with known pulmonary diseases including malignancies, subjects with prior thoracic surgery and subjects that used oral corticosteroids or antibiotics within the prior 3 months, subjects with allergies to study medications and subjects incapable of providing informed consent. Subjects must be in stable condition.

Subjects will be enrolled primarily in the pulmonary function test laboratory, pulmonary and primary care clinics. We will place IRB-approved advertisements in clinics if necessary. Recruitment will occur over a course of 5 years.

The study will have 4 Phases: transition, stability, weaning and surveillance.

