*Phase I: transition from tobacco use to EC (4 weeks):* After signing informed consent, all subjects entering the screening phase will have pulmonary function testing (PFT) if none available in the prior month and we will record basic demographic and social history. After obtaining an initial blood sample (plasma), we will provide and instruct the subjects how to use the EC (eVic®). The nicotine content of the “e-liquid” provided (a PG:VG mix 50:50) will match the number of cigarettes smoked a day and will vary from subject to subject (see below for calculation). We will use the 12 mg/ml concentration e-liquid. During this “transition phase” period we will assess their success of abstaining from smoking tobacco. To monitor abstinence to tobacco smoking, subjects will be seen in person weekly for measurements of exhaled CO (ExCO), and venous COHb. ExCO > 6 ppm (50) or venous COHb >1.6% (51) will be considered the result of tobacco cigarette use. In addition, we will measure urinary marijuana with a qualitative test and if positive we will exclude the subject from the study. During those visits we will assess vaping compliance by downloading the vaping history of the EC using the myVapors® software, available from the EC manufacturer and will collect data regarding potential side effects. Subjects will be encouraged to transition solely to EC within the first 4 weeks. Blood draws for biomarker assessment will be performed in each visit of this phase.

*Phase II: Stability on EC (12 weeks):* In this phase, subjects will remain on EC use for three months. In this phase, all subjects will continue to use ECs at a stable nicotine concentration for additional 12 weeks. Tobacco use abstinence will be monitored every week as in the transition phase as detailed in Table 1. High ExCO levels will be confirmed with venous COHb if necessary. Oral washes and nasal lavages will be done at the beginning and the end of this phase.

Smoker controls: 20 tobacco smokers will be directly enrolled in the “stability” phase, where they will continue to use their regular tobacco for 3 months. They will undergo nasal samplings and NPDs before and after, with monthly blood collections. After this phase, these control subjects may be re-enrolled in the study to start in the transition phase with EC.

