## EXPERIMENTAL METHODS

### PROCEDURES PERFORMED AT THE MIAMI VAMC

Adverse Event recording: We will record information about respiratory symptoms and other potential adverse events. Patients will also receive weekly calls to gather information about tobacco smoking abstinence, symptoms and potential adverse events.

Pulmonary function testing (PFT) will be performed according the American Thoracic Society (ATS) recommendations (52). Participants will be asked to refrain from using short-acting bronchodilators for at least 4 hours before testing if applicable. Lung volumes and  $D_LCO$  will be performed following ATS recommendations (53, 54). Height, weight and oxygen saturation will be measured prior to these tests.

Carboxyhemoglobin (COHb) will be measured in venous blood samples by co-oximetry (pHOx®ULtra, Nova Biomedical, Waltham, MA). Exhaled Carbon Monoxide (ExCO) will be measured by the handheld Smokerlyzer™ device (Covita, UK).

Collection of plasma: Blood samples will be collected in lavender-top tubes and transported to the Pulmonary Research Laboratory at the Miami VA. Plasma will be collected using a standard protocol. A full 8.5 mL of blood will be collected. This will produce about 2.5-3 mL of plasma. Tubes will be centrifuged at 2000-3000 RCF at 4°C for 15 min. Plasma will then be transferred in 1-mL aliquots to pre-labeled cryovials and freezed at -80°C until used. We will use to measure biomarkers and cotinine levels.

Biomarkers: We will measure relevant inflammatory and toxic metabolites in EBC and plasma, including  $H_2O_2$ , 8-isoprostane, IL-8, C-reactive protein, nicotine metabolites, coagulation markers, thiocyanate, acrolein. Subject’s consent will be obtained from participants to store residual samples after analysis for future studies.

Oral washes: Oral washes will be performed by having participants gargle with 10 ml sterile 0.9% saline. These washes will be centrifuged and stored at -80°C for future studies (i.e microbiome).

Leukosorb collection of nasal fluid: After 100  $\mu$ L normal saline will have been sprayed into the nose, a small paper will be inserted and the nostril closed with a nose clip for 2 minutes. Then, the paper will be retracted and eluted for cytokine analysis in the laboratory (56). No adverse effects are known.

[name] PI

ADVERSE AIRWAY EFFECTS OF INHALED NICOTINE FROM TOBACCO AND E-CIGARETTES

VERSION 3.3 09/28/2017

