| PROCEDURE                | enrollment | V1               | V2     | V3     | V4     | V5                             | V6              | V7     | V8     | V9     | V10    | V11    | V12    | V13    | V14    | V15    | V16                     |
| ICF                      | X          |                  |        |        |        |                                |                 |        |        |        |        |        |        |        |        |        |                         |
| baseline questionnaire   | X          |                  |        |        |        |                                |                 |        |        |        |        |        |        |        |        |        |                         |
| FU smoking questionnaire | X          | X                | X      | X      | X      | X                              |                 | X      |        | X      |        | X      |        | X      |        | X      | X                       |
| e-liquid refill          | X          | X                | X      | X      | X      | X                              | X               | X      | X      | X      | X      | X      | X      | X      | X      | X      | X                       |
| Ex CO                    | X          | X                | X      | X      | X      | X                              | X               | X      | X      | X      | X      | X      | X      | X      | X      | X      | X                       |
| venous COHb              | X          | X                | X      | X      | X      | X                              |                 |        | X      |        |        |        | X      |        |        |        | X                       |
| marihuana screen         | X          |                  |        |        | X      |                                |                 |        |        |        |        |        |        |        |        |        | X                       |
| NPD at UM                |            |                  |        |        |        | X                              |                 |        |        |        |        |        |        |        |        |        | X                       |
| nasal lavage             |            |                  |        |        |        | X                              |                 |        |        |        |        |        |        |        |        |        | X                       |

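### Exhaled CO and COHb are measured at enrolment but not used for eligibility, so the CO-based tests cannot show a switch in a light smoker already below both abstinence cut-offs

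*Protocol*

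**What the plan says.** **Entry.** The protocol states the smoking criterion twice. Under Experimental Design: "Subjects that actively smoke and have a history of at least 5 pack-years will be invited to participate". Under Human Subjects, 1. Risks to the Subjects: "We will enroll active smokers older than 18 years, who actively smoke and have a smoking history of at least 5 pack-years". Neither place gives a minimum number of cigarettes per day or a required ExCO, COHb or cotinine value. The 20 continuing smokers are subject to the same exclusions and enter the stability phase directly.

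**Abstinence.** Under Experimental Design, Phase I: "ExCO > 6 ppm (50) or venous COHb >1.6% (51) will be considered the result of tobacco cigarette use". The limits are absolute. They are not compared with the subject's own starting value.

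**Schedule.** Table 1 places ExCO at enrolment and at V1 to V16, and venous COHb at enrolment, V1 to V5, V8, V12 and V16.

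**Other checks.** Success in the transition phase also involves exclusive vaping: "expecting that only one fourth will be able to stay abstinent from tobacco and keep exclusively vaping the ECs after a month". The device log is read: "During those visits we will assess vaping compliance by downloading the vaping history of the EC". Table 1 repeats a smoking questionnaire, and the Miami VAMC procedures add telephone contact: "Patients will also receive weekly calls to gather information about tobacco smoking abstinence, symptoms and potential adverse events". Under Expected Results, Potential Difficulties, and Alternative Strategies: "If there is suspicion that a subject may be smoking, based on interview or equivocal test results, we will opt to exclude the subject".

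**The concern.** Pack-years are cumulative and say little about present intake. A subject can have 5 pack-years behind him and now smoke so little that ExCO stays at or below 6 ppm and COHb at or below 1.6%. For that subject, a negative test at week 4 is what one would have seen without any switch.

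Two results are exposed. The first is the comparison of the 30 e-cigarette users with the 20 smokers: users who still smoke pull the groups together. That direction matters here, because the Expected Results section would read a persistence of smoking-like TGF-β levels as evidence that replacing cigarettes with the device is not less harmful. Undetected smoking in the device group can produce the same picture. The second is the feasibility of switching, a stated secondary outcome, which would be overstated.

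The same gap allows a control with no CO evidence of current smoking to sit in the smoker group, although the protocol gives no particular reason to expect this.

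**Working it through.** **Step 1: what each check can detect in a light smoker below both limits.**
- *ExCO and COHb:* nothing, as long as intake stays at its usual low level.
- *Repetition:* the Expected Results section argues that a smoker may elude one checkpoint but is unlikely to elude all of them. That works if misses are roughly independent. A stable light smoker is missed each time for the same reason.
- *Questionnaire, weekly calls, interview:* these can detect smoking, but they rest on self-report. Payment depends on progress: $100 on qualifying after the first four visits and $200 after the final visit, and the protocol describes the payment schedule as a possible motivation to quit.
- *Puff log:* it shows that the subject vapes, not that he has stopped smoking. No minimum puff count is set.
- *Nicotine and cotinine:* these cannot separate the groups, because the device is meant to match the subject's nicotine intake.
- *Thiocyanate:* it is listed as a biomarker, but no abstinence rule uses it.

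**Step 2: the plan's own figure.** 1. Risks to the Subjects expects about 75% to fail and 120 to be screened: 120 × (1 − 0.75) = 30. This reproduces the planned 30. The figure of about 200 under Experimental Design gives 200 × 0.25 = 50 and does not. I use 120; the percentages below do not depend on the number screened.

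**Step 3: size.** Let *f* be the share of entrants at or below both limits at usual intake. The documents do not give *f*, so it is an assumption shown over a range. Let *p* = 0.25 be the true switching rate in everyone. Worst case: self-report catches none of the non-switchers below the limits.

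- False successes = 120 × *f* × (1 − *p*)
- Apparent rate = (30 + false) / 120
- False share = false / (30 + false)

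| *f* | False successes | Apparent rate | False share | Of 30 in the group |
|---|---|---|---|---|
| 0% | 0 | 30/120 = 25% | 0% | 0 |
| 2% | 1.8 | 31.8/120 = 26.5% | 1.8/31.8 = 5.7% | 1.7 |
| 5% | 4.5 | 34.5/120 = 28.75% | 4.5/34.5 = 13% | 3.9 |
| 10% | 9 | 39/120 = 32.5% | 9/39 = 23% | 6.9 |

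**Step 4: effect on power.** The protocol claims more than 98% power for TGF-β with 30 and 20 subjects but gives no effect size, SD or alpha, so the claim cannot be reproduced. Taking two-sided 0.05 and exactly 98%, the normal approximation Φ(*d*/√(1/20 + 1/30) − 1.96) = 0.98 gives *d* = 1.16. If false switchers do not differ from controls, *d* shrinks by the false share:
- 5.7%: 1.16 × 0.943 = 1.09, power about 97%
- 13%: 1.16 × 0.87 = 1.01, power about 94%
- 23%: 1.16 × 0.77 = 0.89, power about 87%

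**The case against.** The strongest reply is that CO is not the only evidence. Questionnaires, weekly calls, the device log, the exclusive-vaping expectation and exclusion on suspicion all exist. This stands against two inferences a reader might draw. One is that switching is judged by CO alone. The other is that a light smoker passes every abstinence check without switching at all. A subject who never vapes would show in the log, and one who admits smoking can be excluded. What remains is the dual user who vapes, still smokes lightly and does not say so.

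A reader might also infer that anyone with a low enrolment value cannot fail later, whatever he smokes. The documents do not support that. Either value above its limit counts as smoking, and ExCO is taken at every visit, so a subject whose intake rises can be caught. The point covers only those who stay low throughout.

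On size, one could count every low-CO entrant as a false success within a fixed 30. That gives 2.4/30, 6/30 and 12/30, or 8%, 20% and 40%, for *f* of 2%, 5% and 10%. It is too much: it counts genuine switchers among light smokers as false, and it treats the planned 25% as an observed rate that already contains them.

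Finally, an entry gate narrows a study meant to resemble real-world use. That is a fair cost, but a small one. A sensitivity analysis by entry CO would be normal analysis-plan content, so its absence from the protocol is not criticised here.

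**Conclusion.** The point holds in a limited form. The measurement is present at enrolment; what is missing is a rule that uses it. Without one, the objective abstinence tests carry no information for light smokers who remain at or below both limits at usual intake, and the other checks do not fully make up for this.

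The size is unknown, because the documents do not give the share of such smokers. The Step 3 figures of about 6%, 13% and 23% false successes are a worst case. They assume *f* of 2%, 5% and 10%, 25% true switching in everyone, and no detection by self-report. Any detection lowers them, and at *f* = 0 there is no effect. The loss of power further assumes that false switchers look like controls. At small *f* the loss is modest. The bias towards no difference and the inflated switching rate are the better reasons to act. This is a cheap improvement, not a defect that invalidates the design.

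**What to change.** Add to the inclusion criteria, for both groups: ExCO above 6 ppm or venous COHb above 1.6% at the enrolment visit. This is the exact complement of the protocol's own abstinence rule, so every admitted subject starts on the smoking side of the test that will later judge him. State explicitly that the rule also covers controls, since they skip the transition phase and Table 1 does not separate the groups.

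The cost is small. Both tests are already scheduled at enrolment, so no new procedure is needed. A few very light smokers are turned away and generalisability narrows slightly. The gate does not catch a subject who enters just above a limit and later cuts down to below it without stopping, so the interviews, calls and questionnaires are still needed.
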